### Study Population: Eligibility Criteria

Inclusion criteria were (1) age ≥18 years; (2) assigned female sex at birth and identified as a “man, transgender man, or transmasculine”; (3) had sex in the past 3 months with a partner who had a penis and was assigned male sex at birth; (4) access to a smartphone or computer with internet; (5) HIV-negative at baseline (confirmed); (6) reported behavioral HIV risk in the past 3 months, including at least one of the following: (i) receptive vaginal/frontal or anal sex with an assigned male sex at birth partner with a penis; (ii) sharing needles or syringes for illicit drug use or hormones; (iii) self-reported sexually transmitted infection diagnosis; (7) residence in a US EHE-targeted geographic hot spot (48 counties, Washington, DC, San Juan, Puerto Rico—where >50% of HIV diagnoses occurred in 2016-2017—or 7 states with substantial rural HIV diagnoses; see Table S1 in Multimedia Appendix 1); (8) willing and able to provide informed consent in English; and (9) comfortable reading and conversing in English.

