
### HIV Testing, Biomarker-Confirmed PrEP Outcomes, and Specimen Collection Protocol

The primary outcome was biomarker-confirmed PrEP uptake, assessed via emtricitabine triphosphate (FTC-TP) and tenofovir diphosphate (TFV-DP) concentrations in DBS. FTC-TP/TFV-DP assays were used for TFV-containing PrEP regimens approved for this population. PrEP uptake was defined as the detection of any quantifiable drug concentration. Secondary outcomes were PrEP adherence, indicated by TFV-DP concentrations >700 fmol/punch (corresponding to ≥4 doses per week) [54], and PrEP persistence, defined as 2 consecutive DBS samples showing PrEP use. Thresholds were based on the emtricitabine/tenofovir disoproxil fumarate (F/TDF) regimen and adjusted as appropriate for participants using other TFV-containing PrEP formulations (eg, emtricitabine/tenofovir alafenamide, F/TAF).

Participants self-collected DBS samples for HIV testing and PrEP level assessment at baseline, 6, and 12 months. Biospecimen processing was conducted by Molecular Testing Lab (MTL), a CAP-accredited and Clinical Laboratory Improvement Amendments–certified laboratory specializing in at-home specimen collection and processing. Participants provided a mailing address, which was validated through the US Postal Service Address Information application programming interface, and home specimen collection kits were shipped via the US Postal Service. Each kit included detailed visual instructions for specimen collection and a prepaid return mailer. Video instructions were available on the study website to guide participants through specimen self-collection. Each kit included a finger stick device, alcohol wipe, adhesive bandage, a Whatman 5-spot DBS card for HIV testing, and a Whatman 2-spot DBS card for PrEP adherence testing. Participants collected their specimens and returned the cards to the laboratory using the self-addressed, stamped envelope provided in the kit.

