MTL conducted a fourth-generation HIV-1 antigen/antibody ELISA to detect HIV p24 antigen, HIV-1 (groups M and O) antibodies, and HIV-2 antibodies in human blood (sensitivity 100% and specificity 100%) (Molecular Testing Labs, unpublished data, December 2020). Biologic measures of PrEP uptake and cumulative adherence were performed only for participants who self-reported recent PrEP use. HIV test results were typically available within 14 days via the secure MTL portal, reviewed by study staff, and then shared with participants. Positive HIV results were communicated by designated clinical staff, who also contacted participants with positive DBS results to facilitate confirmatory testing. Participants with negative confirmatory results remained eligible for enrollment. PrEP levels were not reported to participants.

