### Randomization and Blinding

Participants were randomized after their baseline HIV results were received and confirmed. Randomization was automated, computer-generated, and allocation sequences were concealed. Stratification was based on ethnoracial identity (BIPOC or Latine vs White) and MAP state LGBTQ equality policy tally (“high, medium, or fair” vs “low or negative” overall policy tally, as of October 2023; see Table S2 in Multimedia Appendix 1) [55]. The MAP state LGBTQ equality policy tally assesses over 50 LGBTQ-related laws and policies across US states (eg, nondiscrimination, health care access, religious exemptions, identity documents), providing a snapshot of the legal and policy climate for LGBTQ people [55]. Stratification was implemented to ensure balance across study arms and to facilitate subgroup analyses [88], given the disproportionate HIV burden among BIPOC or Latine versus White individuals [5] and the impact of repressive anti-LGBTQ policies on HIV prevention efforts [89]. Blinding was maintained at the statistician and investigator levels [90], but was not possible for participants or intervention staff.

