#### Data Analysis by Aim

We describe the planned analyses by aim.

Before analyses, data will be audited for quality and completeness. Descriptive statistics will be calculated, and variable distributions will be evaluated to ensure they meet the assumptions of planned analytic models, including detection of outliers. In this study, *t* tests and chi-square analyses will be used to assess group equivalence at baseline. Variables showing differences across the 4 groups will be considered for inclusion as covariates in the analyses. All analyses will be conducted using SAS (SAS Institute) or R (R Foundation) software, with statistical significance set at an α level of .05.

Aim 1 analyses will follow an intention-to-treat approach. Random-effects logistic regression will be used with PrEP uptake as the primary outcome. The model will include time (baseline, 6, 12, and 18 months), a categorical variable for study condition (PrEP4T, LS4TM, PrEP4T + LS4TM, with SOC as the reference), and the time × study condition interaction to test whether changes in PrEP uptake over time differ across the 3 intervention conditions compared with SOC. Baseline characteristics that differ across study conditions, as well as variables related to missingness, will be included as covariates if necessary. The primary parameter of interest is the time × study condition interaction term; a significant interaction would indicate that the rate of PrEP uptake over time differs between the intervention and SOC groups. Significant interactions will be graphed and interpreted. We hypothesize that PrEP uptake will be highest among participants randomized to condition D (PrEP4T + LS4TM). The same analytic approach will be applied to the secondary outcome of PrEP adherence. PrEP persistence will be assessed at months 12 and 18 using random-effects logistic regression, including time (12 and 18 months), study condition, and the time × study condition interaction. HIV and sexually transmitted infection incidence will be evaluated using logistic regression, with incidence between baseline and 18 months as the outcome and study condition as the predictor.

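### The persistence model has no prespecified baseline PrEP term, which costs precision (not validity) in a secondary endpoint if a material share of participants enter on PrEP

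*Protocol article*

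**What the plan says.** All references are to the protocol article.

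- **Persistence model** (Data Analysis by Aim): "PrEP persistence will be assessed at months 12 and 18 using random-effects logistic regression, including time (12 and 18 months), study condition", together with the time × condition interaction. No baseline level or baseline covariate is named.
- **Uptake model** (same paragraph): "The model will include time (baseline, 6, 12, and 18 months". Baseline is an outcome level there, and adherence follows the same approach.
- **Covariate rule** (same section): "Baseline characteristics that differ across study conditions, as well as variables related to missingness, will be included as covariates if necessary". The section also says that variables found to differ in baseline t tests or chi-square tests will be considered as covariates.
- **Persistence definition** (HIV Testing, Biomarker-Confirmed PrEP Outcomes, and Specimen Collection Protocol): "defined as 2 consecutive DBS samples showing PrEP use".
- **Sampling** (same section): "Participants self-collected DBS samples for HIV testing and PrEP level assessment at baseline, 6, and 12 months". The assay itself is selective: "Biologic measures of PrEP uptake and cumulative adherence were performed only for participants who self-reported recent PrEP use".
- **Eligibility** (Study Population: Eligibility Criteria): nine inclusion criteria, covering among other things HIV status and recent behavioral risk. None concerns current PrEP use.
- **Randomization** (Randomization and Blinding): "Stratification was based on ethnoracial identity (BIPOC or Latine vs White) and MAP state LGBTQ equality policy tally". Baseline PrEP use is not a factor.

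**The concern.** Persistence requires two consecutive positive samples. A participant who enters on PrEP and simply continues therefore counts as persistent in any arm. If such participants are present in number, baseline use should be one of the strongest predictors of this outcome. The trial already collects it, but the model named for persistence does not use it.

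Two things are at stake. The condition comparison is less precise than the collected data allow. And because baseline use is not balanced by design, a chance difference between arms of 75 carries over in part into the estimated effect on persistence. Whether that is corrected is left to a baseline test and a judgement of necessity.

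**Working it through.** **1. The plan's own figures.** No power is stated for persistence, so there is nothing to reproduce for this endpoint. For uptake the article states at least 80% power with 75 per condition and 10% attrition (67.5 per arm). The SOC rate is not given, so this cannot be reproduced exactly. With an absolute 20-point gain at two-sided .05, power is 0.91, 0.84, 0.77 and 0.72 at SOC rates of 5%, 10%, 15% and 20%. The enrollment figure does reproduce: 300/(1 − 0.20) = 375.

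**2. Assumed inputs.** The article gives no share on PrEP at entry (*q*) and no persistence rate in baseline users (*p1*) or in others (*p0*). All figures below rest on assumed ranges.

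**3. Chance imbalance.** The SD of the between-arm difference in baseline use is √(2*q*(1 − *q*)/75), and P(|difference| ≥ 10 points) follows from the normal distribution.

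| *q* | SD | P(≥ 10 points) |
|---|---|---|
| 10% | √(0.18/75) = 4.9 points | 4% |
| 20% | √(0.32/75) = 6.5 points | 13% |
| 30% | √(0.42/75) = 7.5 points | 18% |

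**4. Carry-over.** An imbalance *d* shifts the persistence difference by *d*(*p1* − *p0*). With *p1* − *p0* of 0.45 (60% vs 15%) to 0.65 (80% vs 15%), a 10-point imbalance shifts it by 4.5 to 6.5 points, about half to two-thirds.

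**5. Variance explained.** R² = *q*(1 − *q*)(*p1* − *p0*)²/[P(1 − P)], with P = *q p1* + (1 − *q*)*p0*. For *q* = 20%, *p1* = 80% and *p0* = 15%, P = 0.28 and R² = 0.0676/0.2016 = 0.34. Across the assumed rates R² runs from 0.12 to 0.39.

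**6. Analytic power.** Adjusted power ≈ Φ(z/√(1 − ρ²) − 1.96), with z = 1.96 + z_power. For power 0.80 and ρ = 0.5: 2.802/0.866 − 1.96 = 1.275, giving 0.90. With ρ = 0.3 and 0.4 the results are 0.84 and 0.86.

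**7. Simulated power, month-12 condition effect.** Logistic regression, one arm vs SOC, 75 per arm, conditional odds ratio 3, 4,000 runs. The screened column adjusts only if a four-group chi-square test of baseline use has p < .05.

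| *q* | *p1* / *p0* | No covariate | Screened | Always adjusted |
|---|---|---|---|---|
| 10% | 60% / 15% | 0.77 | 0.78 | 0.81 |
| 20% | 60% / 15% | 0.74 | 0.74 | 0.81 |
| 20% | 80% / 15% | 0.64 | 0.64 | 0.76 |
| 30% | 70% / 10% | 0.50 | 0.51 | 0.69 |

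The gain from always adjusting was about 4 to 19 points over all scenarios run. Screening recovered about 1 point or less, because the test is significant in about 5% of randomizations. With no true effect, rejection was about 0.04 to 0.06 with or without adjustment. The missingness route into the model was not simulated.

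A second set of assumptions used 10% to 40% baseline users, persistence of 70%–80% vs 10%–15% under SOC, gains of 12–15 points in non-users and 0–15 in users, and 1,000 runs. It gave 4 to 15 points for 67 vs 67 and 5 to 22 points for 135 vs 135 (the factorial margin). At 135 vs 135 with 20% baseline users, power rose from 69% to 78%. A further month-12 simulation with 5% to 30% baseline users gave about 5 to 17 points.

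**8. The time × condition term.** A two-visit random-intercept model was simulated with 20%–30% baseline users, baseline log odds ratio 4, intercept SD 1.5–2 and 250 runs per scenario, so each power carries a Monte Carlo SE of about √(0.25/250) = 3 points. With and without the covariate, power for the interaction was 0.27 and 0.26 at 67 per arm. At 135 per side the pairs were 0.60 and 0.55, 0.47 and 0.46, and 0.57 and 0.55. No gain appears. The month-12 condition term in the same model gained 7 to 16 points.

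**The case against.** **Level of detail.** A condensed article may leave the covariates of a secondary model to the analysis plan, and its list of terms does not say that no others are allowed. A reader might infer that the plan rules baseline PrEP out, which it does not. What remains is that the article does fix a covariate rule, and that rule makes adjustment depend on the data. Multiple imputation does not help here, since it fills missing values without putting a predictor into the analysis model.

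**Premise.** A reader might take it as established that the trial enrolled participants already on PrEP. The article gives no baseline PrEP rate, and the table of enrolled participants does not report one. The possibility is inferred from the inclusion criteria, from baseline PrEP testing and from the baseline level in the uptake model. This objection stands, and it is why the size can only be a range.

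**Validity.** A reader might infer that the comparison is biased. Randomization keeps it unbiased on average, and the simulated type I error agrees.

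**Target parameter.** The article names the time × condition term as the parameter of interest for uptake and names none for persistence. The power gains belong to the condition effect and do not carry over to the interaction. This also stands, so the covariate is worth adding only together with a named condition effect.

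**A larger problem in the same sentence.** Persistence is defined by DBS and modelled at month 18, but no 18-month DBS is listed. As written, the two-visit model has no month-18 outcome. This is a separate conflict, but any fix has to respect it.

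**Conclusion.** The point holds as a question of efficiency in a secondary endpoint. The persistence model named in the article omits a baseline measurement that is collected and is likely to be strongly predictive, and the conditional rule recovers almost none of the loss when it works through a baseline test.

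Under assumed shares of 5% to 40% on PrEP at entry, prespecified adjustment is worth roughly 4 to 22 power points for the condition effect. Between arms of 75, an imbalance of 10 points or more has a 4% to 18% chance at shares of 10% to 30%, and about half to two-thirds of it reaches the estimate. The documents do not support a claim of bias, of full carry-over, or of any gain for the time × condition term. If almost nobody enters on PrEP, the benefit disappears.

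The sizes refer to the planned 300. With the 103 reported as enrolled (about 26 per arm), the SD of the imbalance at 20% use would be √(0.32/26) = 11 points. The change is worth making because it costs little, but the analysis is not invalid without it.

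**What to change.** - Add baseline PrEP status to the persistence model as a prespecified fixed covariate, regardless of any baseline test. It cannot be an outcome level, because persistence needs two samples.
- Code it as DBS-confirmed use versus no confirmed use. Participants who report no recent use, and so have no assay, are coded as non-users.
- Name the condition effect on persistence at month 12, from the 6- and 12-month DBS, as the parameter of interest.
- Reconcile the month-18 persistence analysis with the DBS schedule, which ends at month 12.
- Report the standardised (marginal) risk difference from the adjusted model, so that the effect stays comparable with an unadjusted one.

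The cost is a few sentences in the analysis plan and one degree of freedom, with no new data. Without standardisation the reported odds ratio would be conditional on baseline status. The plan should also say that the covariate may be dropped if baseline users are too few to estimate its effect.

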### Assessments and Survey Measures

Participants completed online surveys at baseline and at 3, 6, 9, 12, 15, and 18 months (Figure 2). Comprehensive surveys, lasting approximately 30 minutes, were administered at baseline, 3, 6, 12, and 18 months. The 6-month survey also included an assessment of the intervention program completed after intervention delivery. Short surveys, focused on PrEP uptake and adherence and lasting about 15 minutes, were administered at 9 and 15 months. All surveys were hosted on REDCap, a HIPAA-compliant platform.

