**Figure 2 figure2:**
[figure not shown]
Study schema and flow diagram. DBS: dried blood spot; LS4M: LifeSkills for Men; PrEP4T: PrEP for transgender men and transmasculine people.

Survey measures were guided by the Healthcare Accessibility [49], Gender Affirmation [7,51], and IMB [53] frameworks. Validated measures from transgender populations and prior research were selected to ensure comparability [59-62]. Baseline surveys included both lifetime and past 3-month recall, while follow-up surveys assessed past 3-month recall only. Domains assessed included demographics (age, race, ethnicity, gender identity, sexual orientation, education, income, housing, health insurance), gender affirmation (social, medical, legal), and unmet gender affirmation needs [59,61]. Measures included the PrEP cascade (awareness, indications, uptake, adherence, and persistence, including both daily oral and long-acting injectable formulations) [15,62]; barriers and facilitators to PrEP care [8,62]; PrEP knowledge, motivations, and preferences [8,15,63]; PrEP self-efficacy [64]; and PrEP empowerment [65]. Behavioral risk for HIV acquisition was assessed through sexual partners and practices using an adaptation of the Transmasculine Sexual Health Assessment [66], as well as injection drug use, needle-sharing behaviors, and perceived HIV risk [62]. Sexual partner communication and affirmation were measured using the Sexual Communication Self-Efficacy Scale [67] and the Gender Non-Affirmation from Sexual Partners Scale [14], respectively. Additional questions addressed HIV testing outside the study and sexually transmitted infection screening and diagnoses [61]. Mental health measures included psychological distress (Kessler-6) [68], posttraumatic stress disorder symptoms (Primary Care Posttraumatic Stress Disorder Screen) [69], resilience (Brief Resilience Scale) [70], and use of mental health services (eg, psychotherapy, support groups). Alcohol use disorder was assessed with the Alcohol Use Disorders Identification Test—Consumption [71], substance use disorder symptoms with the Drug Use Disorder Identification Test—Consumption [72], along with categories of drugs used. Discrimination was measured using the Everyday Discrimination Scale [73], which included 14 possible attributions (eg, age, gender identity, race, ethnicity). Internalized stigma [61] was also assessed. Additional measures included health care empowerment [74], health care access, utilization, and mistreatment in health care settings [60]. Social support was assessed with a short form of the Social Support Questionnaire [75], the Trans Community Connectedness subscale of the Gender Minority Stress and Resilience Measure [76], and metrics of social network size [61].

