#### Condition D (SOC + PrEP4T + LS4TM)

This is an online peer-delivered combined intervention. Participants in this arm received both PrEP4*t* (1-on-1) and LS4TM (group-based) interventions in addition to SOC. Group D received a total of 21 hours of content, consisting of six 2-hour LS4TM sessions and six 1.5-hour PrEP4T sessions. These interventions were not delivered simultaneously within the same 6-week period.

**Table 2 table2:** PrEP4T^a^ intervention sessions: session number, title, content, and conceptual framework guiding the intervention sessions.

Session number	Session title	Session content	Conceptual framework
1	Introduction, Background, and Goal Setting	Build rapport with the participant Assess the participant’s background and sexual health history. Set a realistic, sexual health–related goal for the program (eg, to start PrEP^b^, to consistently communicate with partners about sexually transmitted infection testing). Discuss factors that may impact risk for HIV among transgender men and transmasculine people.	IMB^c^ and Gender Affirmation
2	HIV Transmission and Prevention	Assess what participants know about HIV prevention and how they currently put that information into practice. Introduce participants to the concept of harm reduction. Fill in knowledge gaps and answer questions about HIV prevention. Build on or reinforce participants’ existing harm reduction strategies.	IMB and Healthcare Accessibility
3	Accessing PrEP and Preventive Health Care	Discuss barriers to accessing PrEP and work with participants to identify solutions and options available to them. Provide a brief overview of where and how participants can access postexposure prophylaxis. Discuss preventive health care access, with an emphasis on primary care and sexually transmitted infection testing. Address other preventive care topics, including vaccinations (human papillomavirus, hepatitis A and B), contraception, cervical and anal Papanicolaou testing, and gender-affirming care.	IMB and Gender Affirmation Healthcare Accessibility

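### STI incidence is compared by condition using reported diagnoses only, while PrEP4T promotes STI testing, so an arm difference may reflect detection rather than infection

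*Protocol article*

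**What the plan says.** The analysis is given in one sentence under Data Analysis by Aim: "HIV and sexually transmitted infection incidence will be evaluated using logistic regression, with incidence between baseline and 18 months as the outcome". Study condition is the predictor. Nothing else is said about how the STI outcome is built.

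The data source is described under Assessments and Survey Measures: "Additional questions addressed HIV testing outside the study and sexually transmitted infection screening and diagnoses". The specimen section covers other tests: "Participants self-collected DBS samples for HIV testing and PrEP level assessment at baseline, 6, and 12 months". The kit holds one card for HIV and one for PrEP level, and no STI specimen is listed.

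Table 2 gives this as part of PrEP4T session 3: "Discuss preventive health care access, with an emphasis on primary care and sexually transmitted infection testing". Session 1 of the same intervention offers talking with partners about STI testing as an example goal. Table 3 (LS4TM) and the description of Condition A do not name STI testing. They refer to sexual health in general terms.

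**The concern.** Incidence is the rate at which infections occur. With no scheduled STI test, the study sees only infections that someone looked for outside the study, and one of the two randomized factors encourages participants to look. Conditions B and D receive that encouragement; A and C do not, as far as the article says. The introduction reinforces the expectation, since it credits peer navigation with more linkage to medical services.

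If PrEP4T does raise testing, its arms will report more diagnoses at the same true infection rate. A real fall in STIs could then disappear, or better care could be reported as harm. The survey collects STI screening, but the stated analysis gives that item no role.

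**Working it through.** The article states no STI rate, testing rate or power for this outcome, so there is no figure to reproduce. Everything below is an illustration on assumed inputs.

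**Basic model.** Observed risk = true risk × probability of being tested, with a participant who reports no diagnosis counted as having none. Odds ratio = [p1/(1−p1)] / [p0/(1−p0)], where 1 is a PrEP4T arm and 0 a non-PrEP4T arm. True risk is 15% in both.

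| Tested, without vs with PrEP4T | Observed risk | Spurious odds ratio |
|---|---|---|
| 50% vs 60% | 7.5% vs 9.0% | 1.22 |
| 50% vs 70% | 7.5% vs 10.5% | 1.45 |
| 40% vs 60% | 6.0% vs 9.0% | 1.55 |
| 40% vs 70% | 6.0% vs 10.5% | 1.84 |

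Worked case, 40% vs 60%: 0.15 × 0.40 = 0.06; 0.15 × 0.60 = 0.09; (0.09/0.91)/(0.06/0.94) = 1.55. With equal testing the odds ratio is 1.00.

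**Some infections diagnosed in any arm.** Let a share s be diagnosed whatever the arm (symptoms, partner notification). Observed risk = true risk × [s + (1−s) × probability tested].

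- 40% vs 60%: s = 0.3 gives 8.7% vs 10.8%, odds ratio 1.27; s = 0.5 gives 10.5% vs 12.0%, odds ratio 1.16.
- 40% vs 70%: s = 0.3 gives 8.7% vs 11.85%, odds ratio 1.41; s = 0.5 gives 10.5% vs 12.75%, odds ratio 1.25.

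**Masking.** Suppose true risk falls from 20% to 15% with testing of 50% vs 70%. Observed risk is 0.20 × 0.50 = 10.0% vs 0.15 × 0.70 = 10.5%. The true odds ratio of 0.71 appears as 1.06.

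**Chance of a spurious significant result.** The comparison is one condition against another, with 75 per arm less the article's 10% attrition: 75 × 0.9 = 67.5, about 68. Using a two-sided 0.05 two-proportion test (normal approximation, both tails counted), rejection with no true effect is about 6% to 16% over the table above. At 25% true risk and 40% vs 70% testing it reaches about 24%.

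**What the sensitivity analysis would show.** Take 40% vs 60% screened, 15% positivity among the screened, and assumed positivity q in the unscreened. Risk = 0.06 + 0.60q vs 0.09 + 0.40q.

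- q = 0: 6% vs 9%, odds ratio 1.55
- q = 5%: 9% vs 11%, odds ratio 1.25
- q = 10%: 12% vs 13%, odds ratio 1.10
- q = 15%: 15% vs 15%, odds ratio 1.00

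The conclusion thus depends on q, which the planned model leaves unstated.

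**Coverage of the window.** "follow-up surveys assessed past 3-month recall only", and the comprehensive surveys "were administered at baseline, 3, 6, 12, and 18 months". They cover months 0–6, 9–12 and 15–18. Months 6–9 and 12–15 are covered only if the short surveys ask about STIs, which the article does not say ("Short surveys, focused on PrEP uptake and adherence and lasting about 15 minutes, were administered at 9 and 15 months"). This applies to all arms alike, but it is a further reason not to call the outcome incidence over 18 months.

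**The case against.** The best reply is that a condensed article can leave the coding of an additional endpoint to the SAP, and that the screening item is already collected. That is fair for the coding rule: the article does not say that unscreened participants are scored as free of STI. It does name the outcome as incidence and compare it directly by condition, from a data source that records diagnoses.

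Other parts of the reply also stand. The testing gaps are assumed, and the encouragement is one item in one of six sessions. All arms receive sexual health materials, and LS4TM session 6 covers general sexual health. At 50% vs 60% the spurious rejection rate at 68 per arm is close to nominal. The basic model overstates the distortion if many infections are diagnosed in any arm.

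Some stronger readings are tempting but unsupported:

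- A reader might infer that the outcome can be scored only in tested participants. Every survey respondent can be scored; what requires a test and a diagnosis is being counted positive.
- A reader might pool the arms by factor (135 per side) and quote false-positive rates up to 43%. The article names study condition as the predictor, so the single-arm figures above are the relevant ones.
- A reader might extend the point to HIV. All arms are offered the same home HIV test at the same visits, so that half of the sentence is less exposed.
- A reader might want to limit the analysis to screened participants. Screening occurs after randomization and may be affected by treatment, so this would add selection bias and leave intention-to-treat.

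**Conclusion.** The concern holds as a risk of arm-dependent detection. The plan as written compares diagnosed STIs under the name of incidence, and PrEP4T alone is described as encouraging STI testing. The likely direction is toward more recorded STIs in B and D. The size cannot be determined from the article. Under the assumptions shown, the spurious odds ratio is about 1.2 to 1.8 at 15% true risk, and about 1.2 to 1.4 for the two wider testing gaps if 30% to 50% of infections are diagnosed regardless of arm.

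It would be too strong to say that the contrast is certainly biased or that the trial's main conclusions are affected. No testing rates are given, and STI incidence is neither the primary outcome (PrEP uptake) nor a named secondary outcome (adherence, persistence).

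**What to change.** 1. Keep all randomized participants in the intention-to-treat comparison, and do not restrict the main analysis to those screened.
2. Define and report the outcome as self-reported diagnosed STI, and state which survey months it covers.
3. Tabulate STI screening by condition from the item already collected.
4. Add a sensitivity analysis over a stated range of positivity in unscreened participants, allowed to differ from positivity in the screened.
5. State that an arm difference will not be interpreted as a difference in STI incidence when screening differs by condition.

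The cost is a change of wording, one table and one sensitivity analysis, with no new data. The drawback is a more cautious and less precise STI conclusion. The grant ended with 103 enrolled of the 300 planned, so the change applies to any analysis of the data collected and to a successor trial.
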